#### Safety and adverse events

To determine the safety of the intervention, adverse events that occur as a result of the intervention will be recorded. Any injuries or symptoms developed directly as a result of the exercises will be recorded as an adverse event. Volunteers will be trained to document any adverse events and report it back to the research team. The clubs also have well established procedures for responding to incidents and accidents including access to emergency contacts of participants.

### Acceptability of the intervention

Interviews will be conducted with older adults, their family members or carers, volunteers, and those involved in recruiting participants and training volunteers, to determine the acceptability of the training and the intervention and to explore barriers and enablers to the implementation of the intervention. Interviews will be semi-structured to help guide conversation while allowing participants the flexibility to elaborate and reflect on any meaningful experiences.^34^ The interviews will be conducted by a member of the research team (SM) who is experienced in qualitative interviews. The interviews will be conducted within the first 2 months of the exercise groups to understand how the intervention is being delivered and whether any modifications to the intervention are needed. Further interviews will be conducted towards the end of the study period (at 6 months) to understand stakeholders’ lived experience with the intervention and to explore barriers and facilitators for engagement and delivery of the intervention. This will ensure that participants’ views are captured during the earlier stages of the intervention, and when the groups are well established.

Older adults will be selected by purposive sampling to share their thoughts and views regarding the implementation of the volunteer-led physical activity session.^35^ To ensure that a wide range of views are included in the interviews, participants will be selected to include male and female participants, different clubs, and a representative age range. The aim is to interview at least two participants per club, with a total number of 10 participants. Family members and carers (n=5) of the exercise participants will also be invited to participate in the interviews. Their views and experience will provide valuable insight into the acceptability of the intervention and the potential barriers and enablers for a future wider implementation. All interviews will be conducted via telephone or online (eg, Zoom, Skype) depending on participant preference.

Semi-structured interviews will also be conducted with volunteers leading the intervention. Discussions among volunteers are likely to generate a wider perspective of the implementation process and may provide insight into the group narrative on their experiences in delivering the intervention and their interaction with the research participants.^36 37^ The aim is to interview at least one volunteer from each club, with a total number of five volunteers.

The semi-structured interviews will consist of several key open-ended questions that help define the areas explored but allow the interviewer or interviewee to expand and diverge with the aim of pursuing or developing an idea with more depth. The interview schedules will be underpinned by normalisation process theory (NPT).^38^ The interviews will be audiorecorded for data collection purposes.

#### Normalisation process theory

The NPT provides a set of sociological tools to understand and explain the social processes through which new or modified practice of thinking, enacting and organising work are operationalised in healthcare and other institutional settings.^38^ The use of an implementation theory is useful as it helps researchers identify, describe and explain important elements of the implementation process.^39^ NPT was chosen as the framework that underpinned this study as it was systematic in its approach, easy to understand and provided a structured framework to evaluate the implementation process of this study. The online toolkit available for this implementation theory also made the application of NPT convenient and practical.^40^ The interview schedules were developed based on the four components of NPT:

Coherence: meaning and sense-making.Cognitive participation: this explores the likelihood of all participants being committed and engaged with the intervention.Collective action: the consideration of the work that participants do to make the intervention function.Reflexive monitoring: which involves participants appraising or reflecting on the intervention.

The questions will be framed to explore each component of the NPT in greater detail, with the aim to determine factors that facilitated or inhibited these four key processes which are essential for successful implementation and adoption of the intervention. The first section of the interview guide will focus on interviewees’ views on the relevance and importance of physical activity in general, and in particular, the online exercises. Next, participants’ views on factors that encouraged or prevented them from being committed and engaged with the online group exercise will be explored. Volunteers, staff members, older adults, and their carers’ experience of the exercise group and how the stakeholders interacted with each other will then be explored to better understand the impact of the group dynamics on the intervention. Interviewees will then be encouraged to reflect on what worked well with the intervention and explore aspects within the intervention that could be improved or require modification.

### Data analysis plan

#### Quantitative data analysis

Data collected will be double entered into a secured database for analysis. Statistical analysis will be conducted using the statistical software SPSS Statistics V.25. Descriptive statistics—median (IQR); mean (SD); number (%)—will be used to analyse the numbers of volunteers recruited, trained, and retained, as well as the type and extent of progression of the seated exercise, and duration of their activity, and patients’ adherence to the intervention. Analysis of the above outcome measures will be used to develop an assessment of the feasibility of delivering this intervention. Adherence to the intervention and reasons for non-adherence will be reported.

Outcome measures recorded at baseline will be compared with measurement at 6 months to determine if the PA intervention had an impact on physical activity levels measured by CHAMPS, functional outcomes including performance in ADLs (Barthel Index), quality of life (EQ-5D-5L), frailty status (PRISMA-7) and sarcopenia status (SARC-F). The distribution of each outcome measure will be assessed for normality. Depending on the skew of the data, parametric (t-test) or non-parametric (Mann-Whitney U test) statistics will be used for continuous variables. χ^2^ test will be used for categorical variables.

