### Participant recruitment

#### Volunteer recruitment

The research team will be invited by club staff to attend the virtual clubs to introduce the study. Club volunteers and members who are interested in leading the group exercise will indicate their interest to staff members or approach the research team directly. To lead the group exercise, volunteers must be physically able to perform the exercises themselves and be able to provide written consent. This will be assessed at the training sessions by the trainer (SM).

The participant information sheet and the consent form will be sent through the post. Club members are invited to contact the research team for further discussions about the study. Once the research team has received the signed consent form, volunteers will be invited to participate in the online training. To deliver online group exercise to 30 exercise participants, it is estimated that at least 12 volunteers will be needed to lead 6 online groups. Volunteers will be paired up to lead and deliver the intervention.

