#### Exercise participant recruitment

Club members who are interested in participating in the online group exercise will indicate their interest to club staff or approach the research team directly. Participant information sheet and consent forms will be posted to club members.

The inclusion criteria for the group exercise participants are: adults aged 65 years and older, able to walk with or without a walking aid, and able to provide written consent (box 1). Participants who are actively participating in other online exercise classes will be excluded. The aim is to recruit 30 older adults attending social clubs who do not engage in regular exercise.

Box 1Inclusion and exclusion criteriaInclusion criteriaOlder adults aged >65 years.Able to walk, with or without a walking aid.Able to provide written consent.Exclusion criteriaActively participating in other online exercise classes.

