#### Primary outcomes

The primary outcome of this study is the feasibility of implementing volunteer-led online group exercise for older adults. This will be assessed by determining:

The number of volunteers recruited, trained and retained at the end of the study.The number of physical activity sessions delivered and completed by participants (adherence).The fidelity of the exercise intervention delivered by volunteers.

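### The primary feasibility results from about 12 volunteers and 30 participants are planned without intervals, and 30 participants cannot determine safety

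*Protocol article*

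**What the plan says.** Under Primary outcomes, the protocol article makes feasibility the primary outcome. It is judged by three things: "The number of volunteers recruited, trained and retained at the end of the study", the sessions delivered and completed by participants (adherence), and the fidelity of delivery.

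Under Quantitative data analysis the method is named: "Descriptive statistics—median (IQR); mean (SD); number (%)—will be used to analyse the numbers of volunteers recruited". The same sentence goes on to volunteers trained and retained, progression and duration of the exercise, and adherence. The next sentence bases the feasibility assessment on this analysis. The Abstract likewise gives simple descriptive statistics for feasibility. For the secondary outcomes the same section plans a t-test, Mann-Whitney U test or χ² test. The article mentions no confidence interval, precision target or feasibility threshold.

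The sizes come from the recruitment sections. For volunteers, "it is estimated that at least 12 volunteers will be needed to lead 6 online groups", and "Volunteers will be paired up to lead and deliver the intervention". For participants, "The aim is to recruit 30 older adults attending social clubs who do not engage in regular exercise".

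On safety, the section Safety and adverse events says: "To determine the safety of the intervention, adverse events that occur as a result of the intervention will be recorded". It does not say how the events will be summarised.

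**The concern.** A number with a percentage, a mean with its SD or a median with its IQR describes the people observed. None of them shows how precisely so few people estimate an underlying rate. Here that matters for the primary outcome, on which the study's main conclusion rests, whereas the secondary outcomes do get inferential methods.

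The stated purpose, under Strengths and limitations, reaches beyond these clubs: the results are to inform a toolkit for wider use and a future controlled study. Anyone planning volunteer numbers for new clubs would want to know whether a retention of 83% could reasonably be near one half.

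The safety sentence is a separate matter of wording. It gives the recording of events a purpose that 30 participants cannot serve, even if every session passes without an event.

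**Working it through.** **Inputs.** Six online groups, volunteers in pairs, and a minimum of 12 volunteers (Volunteer recruitment). 30 participants (Exercise participant recruitment). The article gives no expected retention, adherence or event rate, so every count below is an assumption, shown over a range.

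**The plan's own figure.** 6 groups × 2 volunteers = 12, which agrees with the article. 30 / 6 = 5 participants per group. The 30 has no stated statistical derivation, so there is nothing to reproduce.

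**Exact 95% intervals.** Clopper-Pearson for x of n: the lower limit is the 2.5% point of Beta(x, n − x + 1) and the upper limit is the 97.5% point of Beta(x + 1, n − x).

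| Assumed result | Estimate | Exact 95% interval |
|---|---|---|
| Volunteers retained 8/12 | 67% | 35% to 90% |
| 9/12 | 75% | 43% to 95% |
| 10/12 | 83% | 52% to 98% |
| 12/12 | 100% | 74% to 100% |
| Participants 21/30 | 70% | 51% to 85% |
| 24/30 | 80% | 61% to 92% |
| 27/30 | 90% | 73% to 98% |

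The method of interval matters little: Wilson limits for 10/12 are 55% to 95%.

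**Chance of a good-looking count under a poorer rate.** If true retention were 60%, 10 or more of 12 would be retained with probability 0.083. If it were 50%, 9 or more of 12 would be retained with probability 0.073.

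**Zero adverse events in 30.** The upper limit of the two-sided 95% interval is 1 − 0.025^(1/30) = 11.6%, about one participant in nine. The one-sided 95% bound is 1 − 0.05^(1/30) = 9.5%. If the true rate were 5%, no event would be seen with probability 0.95^30 = 0.21.

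**Clustering by group.** With 5 participants per group the design effect is 1 + (5 − 1) × ICC, and the effective sample size is 30 divided by it. The article gives no ICC, so these values are assumed:

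| ICC | Design effect | Effective n | Interval for 80% | Upper limit, no events |
|---|---|---|---|---|
| 0.05 | 1.2 | 25.0 | 59% to 93% | 13.7% |
| 0.10 | 1.4 | 21.4 | 57% to 94% | 15.8% |
| 0.20 | 1.8 | 16.7 | 54% to 95% | 19.9% |

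**More volunteers than the minimum.** With 24 volunteers, 20 retained is again 83%, with an interval of 63% to 95%: narrower, but still wide.

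**The case against.** The strongest reply is that descriptive analysis is usual in an uncontrolled feasibility study, and that adding an interval to a percentage is a detail that a fuller plan may hold. Much of that stands. Number (%) is not wrong, the article does not exclude intervals, and a reader given the count and its denominator can compute one. But the article does choose a method for its primary outcome and rests the feasibility assessment on it, and that method shows no precision. An interval is estimation and fits a descriptive aim.

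Several stronger readings are tempting and are not supported:

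- That safety, too, is planned as bare numbers and percentages. The analysis sentence does not mention adverse events, and the safety section says only that they will be recorded. The safety point rests on the stated purpose alone.
- That the results will be over-read. This predicts conduct that the article does not state; *may* is as far as one can go.
- That the data would fit clearly unfavourable rates. With no threshold stated, nothing defines unfavourable, and the counts above are hypothetical.
- That conclusions must be worded from the unfavourable limit. That is a preference. Even 12/12 has a lower limit of 74%, with no benchmark to set it against.
- That the toolkit depends on a retention percentage. Under Qualitative data analysis it is built from the training material, exercises, checklists and implementation information, drawing on the interviews. The future sample size, under Study design, is tied to the physical activity and functional measures.

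Two further limits stand. Not every primary outcome is a proportion: volunteers recruited and sessions delivered are counts, and adherence is sessions per person, so 24/30 illustrates precision and is not an outcome that the article defines. Also, a plain exact interval assumes independent people, whereas volunteers work in pairs and participants in groups. And since clubs and volunteers come forward themselves, no interval of this kind covers differences between these clubs and others.

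**Conclusion.** The point holds as a modest improvement to a stated method. With the minimum of 12 volunteers, a retention of 83% would be compatible with anything from 52% to 98%. With 30 participants, 80% would be compatible with 61% to 92%, and wider if results cluster by group. A favourable percentage given alone may be over-read. Separately, recording events in 30 people cannot determine safety: no event at all leaves an upper limit of 11.6%, or about 14% to 20% under an assumed ICC of 0.05 to 0.20.

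These sizes rest on assumed counts, on 12 being a minimum, and, outside the clustering table, on independent observations. No number stated in the article is wrong.

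**What to change.** Under Quantitative data analysis:

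- Report a 95% interval with each feasibility outcome that is a true proportion, for example an exact interval for the proportion of trained volunteers who are retained.
- Report mean per-person adherence with a 95% interval. Leave plain counts, such as volunteers recruited, as counts.
- Allow for clustering by exercise group, or state that the interval ignores it.
- Report the proportion of participants with an adverse event together with its upper confidence limit.
- Say that feasibility will be interpreted with these intervals in view.

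Under Safety and adverse events, replace the aim of determining safety with that of describing adverse events.

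The cost is a few lines of text, a little more analysis and conclusions that look less favourable. No further participants, data or changes to the design are needed.

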#### Secondary outcomes

The secondary outcome measures include measurement of physical activity levels and performance of activities of daily living (ADLs). Physical activity levels will be measured using the Community Health Model Activities Programme for Seniors (CHAMPS) questionnaire.^23^ The questionnaire assesses self-reported weekly frequency and duration of various physical activities typically undertaken by older adults, and is a validated measure of physical activity for older people.^24^ Performance of ADL will be measured using the Barthel Index.^25^ The Barthel Index measures ADL including transfers, walking, stairs, toilet use, dressing, feeding, bladder control, bowel control, grooming and bathing, to give a maximum total score of 100. It is a validated measure of ADL that is recommended for use in research among older people.^26^ TheEuroQol - 5 Dimension (EQ-5D-5L) measure developed by the EuroQol group will be used to determine health-related quality of life.^27^ The measure comprises five dimensions: mobility, self-care, usual activities, pain/discomfort, and anxiety/ depression. Each dimension is given a 1-digit score and the digits for the five dimensions are combined unto a 5-digit number that describes the patient’s health state. The measure is commonly used in research among older people.^28 29^ The Strength, Assistance with walking, Rising from a chair, Climbing stairs, and Falls (SARC-F) questionnaire will be used as a measure to assess for sarcopenia.^30^ According to recent guidelines from the European Working Group on Sarcopenia in Older People, SARC-F is the recommended tool for sarcopenia case finding.^31^ It comprises five components: strength, assistance in walking, rise from a chair, climbing stairs and falls. The scores range from 0 to 10, with a score of equal to or greater than four being predictive of sarcopenia and poor outcome. Program of Research to Integrate Services for the Maintenance of Autonomy (PRISMA-7) screening tool will be used to characterise participants’ frailty status.^32^ The questionnaire contains seven items with a positive score of three or more indicating frailty. The PRISMA-7 tool has been shown to have high accuracy in identifying frail older adults in the community setting.^33^

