These outcome measures will be recorded at baseline, using remote assessment formats (eg, telephone based) and repeated at 6 months. Cost analysis will be conducted to determine the cost of implementing this intervention. The analysis will include the cost of training the volunteers, taking into consideration the time needed to deliver the group training sessions and the individual competency assessments, and the provision of training materials.

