#### Strengths and limitations of the study

This study explores a novel approach of training volunteers to deliver online group exercise to older adults. Application of a mixed-methods approach in this study will help determine the feasibility of the intervention and explore barriers and facilitators to a successful implementation of the intervention. However, a limitation of the study is the lack of a control group. Recruitment of older adults will be through established social clubs, in which recruiting some older adults and excluding others from participating in the exercise groups would be a challenge. Additionally, as this is a feasibility study, we will use a range of social clubs of varying sizes, and client groups with different age ranges and physical abilities, to explore different approaches to the intervention rather than including a control group. Nevertheless, this study has been designed to assess the feasibility and acceptability of the intervention with a view to informing the development of a toolkit to support the wider implementation of the intervention and a future controlled experimental design. This study excluded older adults who are not able to walk. Patients who are bed-bound will not be able to participate in the seated exercises without additional support. This additional support cannot be met by this study. As the intervention is delivered remotely, participants must have a level of independence to participate safely. Additionally, one of the key outcome measure is physical activity levels and older adults who are bed-bound will have minimal activity levels.

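### Baseline and 6-month outcomes in the same participants are compared with independent-sample methods, so a change in who is measured can pass for a change in health

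*Protocol article*

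**What the plan says.** Protocol article, Quantitative data analysis: "Outcome measures recorded at baseline will be compared with measurement at 6 months to determine if the PA intervention had an impact". The outcomes are CHAMPS, Barthel Index, EQ-5D-5L, PRISMA-7 and SARC-F. Depending on skew, "parametric (t-test) or non-parametric (Mann-Whitney U test) statistics will be used for continuous variables", and a chi-square "test will be used for categorical variables". No paired method is named, and the t-test is not described as paired or unpaired.

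On data collection, Secondary outcomes says: "These outcome measures will be recorded at baseline, using remote assessment formats (eg, telephone based) and repeated at 6 months". On people who attend less or stop, the analysis section says: "Adherence to the intervention and reasons for non-adherence will be reported". The article states neither that the 6-month assessment is limited to people still attending nor that it continues after someone stops.

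The design has one group. The article concedes that "a limitation of the study is the lack of a control group". Under Study design, the measured impact is meant to help inform the sample size of a later effectiveness trial.

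**The concern.** Each participant is their own comparison, so the natural estimate is the change within a person. A paired analysis uses only people seen twice and so compares like with like. Mann-Whitney U and chi-square take two columns that need not hold the same people. Followed as written, anyone without a 6-month value can contribute to the baseline column only.

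This affects the estimate as well as the p-value. With complete follow-up, the difference in means is the same whether or not the data are paired. With incomplete follow-up it is not, and the two columns differ in composition.

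If the people missing at 6 months were frailer or less active at baseline, scores such as Barthel would appear to rise and the proportions frail or sarcopenic to fall, even if nobody changed. If fitter people were missing, the error would run the other way. There is no control arm to show that a difference came from composition. An inflated change carried into a later sample size calculation would make that trial too small.

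**Working it through.** The article gives no dropout rate, Barthel distribution, frail share or sample size calculation, so the plan has no figure of its own to reproduce.

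**Inputs from the article**
- Number of participants: "The aim is to recruit 30 older adults attending social clubs who do not engage in regular exercise" (Exercise participant recruitment).
- Frailty cut-off: "The questionnaire contains seven items with a positive score of three or more indicating frailty" (Secondary outcomes).
- Tests as quoted above; no control group.

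**Assumptions**
- Nobody's health changes.
- 3, 6 or 9 of 30 (10%, 20%, 30%) lack a 6-month value.
- Those lost score 5 or 15 Barthel points below those kept.
- 30%, 40% or 50% are frail at baseline.

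**Step 1: shift in a mean.** Let p be the proportion lost, S the mean of those kept and L the mean of those lost. The baseline mean of everyone is (1 − p)S + pL, and the 6-month mean is S. The apparent change is S − [(1 − p)S + pL] = p(S − L).

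| Gap S − L | p = 0.10 | p = 0.20 | p = 0.30 |
|---|---|---|---|
| 5 points | 0.5 | 1.0 | 1.5 |
| 15 points | 1.5 | 3.0 | 4.5 |

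If the gap is zero, the shift is zero.

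**Step 2: shift in the proportion frail.** If everyone lost was frail (the extreme case), the 6-month share is (frail at baseline − lost)/(30 − lost). The p-values are from the uncorrected chi-square test of all 30 at baseline against those left.

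| Baseline | 3 lost | 6 lost | 9 lost |
|---|---|---|---|
| 9/30 = 30.0% | 6/27 = 22.2% (p = 0.506) | 3/24 = 12.5% (p = 0.124) | 0/21 = 0.0% (p = 0.006) |
| 12/30 = 40.0% | 9/27 = 33.3% (p = 0.602) | 6/24 = 25.0% (p = 0.245) | 3/21 = 14.3% (p = 0.047) |
| 15/30 = 50.0% | 12/27 = 44.4% (p = 0.675) | 9/24 = 37.5% (p = 0.358) | 6/21 = 28.6% (p = 0.126) |

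Less extreme cases, from 12/30 = 40.0% with 6 lost: if 5 of the 6 were frail, 7/24 = 29.2%; if 3 of the 6 were frail, 9/24 = 37.5%.

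**Step 3: simulation of a standardised score.** n = 30, higher is better, no mean change, assumed test-retest correlation 0.8, and correlation of 0.3, 0.5 or 1.0 (the extreme) between baseline score and staying in.

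| Lost | All baseline v those kept: apparent gain (SD) | Paired change in those kept (SD) |
|---|---|---|
| 3 | 0.045 to 0.149 | −0.010 to −0.038 |
| 6 | 0.081 to 0.269 | −0.022 to −0.071 |
| 9 | 0.115 to 0.382 | −0.029 to −0.100 |

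**Step 4: the same data, paired.** In the frailty counts the change is exactly 0: with 12 frail at baseline and 6 lost, the share is 6/24 at both times. In the simulation the false gain disappears. A small unfavourable shift from regression to the mean remains. Pairing removes the change in who is counted; it does not show what happened to the people who were lost.

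**The case against.** A reader might infer that the plan sets every baseline value against every 6-month value, and that people who leave the classes stay in the first column and vanish from the second. The article says neither. Saying that the measures are repeated at 6 months can be read as covering everyone, and if everyone is assessed this bias does not arise. Nor does the stated reporting of non-adherence imply loss to assessment: under Primary outcomes, adherence concerns sessions completed, and a remote assessment does not depend on class attendance.

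Follow-up of people who stop, analysis sets and missing-data rules are commonly left to a full protocol or SAP. Neither is shown, so silence on them is not a fault.

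The magnitudes rest on chosen inputs. Participants must be able to walk and have some independence, so a 15-point Barthel gap may be large. Even with every lost participant frail, nominal significance appears only at 30% loss, and only with 30% or 40% frail at baseline. The outcomes are secondary, and the missing control group is already acknowledged.

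All of this stands and limits the weight. It does not remove the stated choice of test. Mann-Whitney U and chi-square are named for repeated measurements on the same people, which is a choice in the text and not an omission. It leaves the estimate open to a change in composition as soon as follow-up is incomplete.

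**Conclusion.** The point holds in a limited form. The article fixes independent-sample methods for a within-person comparison and leaves the t-test unspecified. If some of the 30 participants lack a 6-month value and differ from the rest at baseline, the reported difference will combine real change with altered composition, and there is no control group to separate the two.

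The size is illustrative. With 10% to 30% lost and no true change, the shift is 0.5 to 1.5 Barthel points for a 5-point gap and 1.5 to 4.5 for a 15-point gap. The loss rates, the gaps, the frail shares and the direction of selection are all assumptions. The article does not support a claim that people who stop are lost to follow-up, or that such a bias will occur.

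The consequence is modest because feasibility is primary. The correction is still worth making, since the pre-post results are to be read as impact and used in planning a later trial.

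**What to change.** In Quantitative data analysis, replace the stated tests with an estimate of change within participants who have both measurements: paired t-test or Wilcoxon signed-rank test for continuous outcomes, and McNemar's test for two-category outcomes such as frail or not. Report the baseline and 6-month summaries for those same people, with their number. Changing the test alone is not enough if the tabulated means and percentages still come from different people.

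As clarifications only:
- In Secondary outcomes, confirm that the remote 6-month assessment is attempted regardless of class attendance, unless the participant declines contact.
- Show baseline values for those with and without a 6-month value, because pairing alone says nothing about those lost.

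The cost is a sentence or two, one descriptive table and perhaps a few telephone calls. The comparison may rest on slightly fewer people at baseline, and the observed change may look less favourable.
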